### Description of sample

Teeth will be selected from male and female children 6–10 years of age with no distinction as to ethnicity enrolled for outpatient treatment at the Aria College in the city of Brasília with first molars that have MIH and restorative treatment need. The study has received a letter of approval from Aria College, granting permission for the research to be conducted in the Department of Pediatric Dentistry at their facility. Individuals who met the eligibility criteria will immediately be randomized and treated. Each participant will receive treatment on a single molar affected by MIH. In cases where more than one tooth meets the eligibility criteria, the tooth to be included in the study will be selected randomly through a simple lottery method. This selection process will occur prior to the randomization of the interventions to ensure a clear and unbiased allocation of treatments. The trial will be reported following the CONSORT guidelines.

### Inclusion criteria

Male and female children;6–10 years of age;At least one permanent first molar with MIH (codes 5 and 6 of molar-incisor hypomineralization severity scoring system (MIH-SSS) [20]Presence of hypersensitivityDirect viewing and access.

### Exclusion criteria

Clinically: signs or symptoms of pulp involvement;Radiographically: evidence of pulp involvement (initial periapical radiograph);Teeth with MIH with no indication for direct restorative treatment (multiple surfaces associated with large extensions) [21].Partially erupted teeth;Previous restorative treatment.Patients who have undergone previous desensitizing treatments

### Involvement of patient and public

The guardians of the patients will not be involved in the design of the study. After data analysis, the guardians will have the opportunity to participate in a meeting during which the results will be shared. The statement of informed consent signed by the guardians of the study will explain that confidentiality of the data will be ensured.

### Sample size calculation

The sample size will be estimated using the G*Power software (version 3.1, Franz Faul, Unikiel, Germany) [22] for a priori repeated measures ANOVA. An effect size of 0.352, derived from the group mean dispersions reported in the literature [23], will be considered. The alpha error will be set at 0.05, statistical power at 80%, and the design includes 3 groups and 5 repeated measures. The final calculation indicates the need for 66 individuals in total, corresponding to 22 participants per group. To increase the robustness of the results and compensate for potential dropouts, the sample will be inflated by 15%, resulting in 25 individuals per group and a total of 75 participants.

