### Randomization

The participants will be randomly allocated to the different groups using block randomization. A computer-generated sequence (random.org; Randomness and Integrity Services, Dublin, Leinster, Ireland) will be used to allocate each participant to a specific group maintaining a 1:1:1 proportion (equal number of participants in all groups). Randomization will be performed in 5 blocks, with 15 participants per block, totaling 75 participants across the study. Allocation concealment will be ensured with the use of sequentially numbered sealed opaque envelopes.

Teeth selected for treatment will be randomized into three groups:

**Group 1**: Photobiomodulation + restoration with self-cure composite resin

**Group 2**: Restoration with self-cure composite resin

**Group 3**: Photobiomodulation + restoration with photopolymerizable bulk-fill composite resin

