### Statistical analysis

The data will be presented using descriptive statistics. Continuous variables will be described with mean and standard deviation, and categorical variables by relative frequency. Statistical analyses will be conducted using SPSS software (version 28.0, IBM, USA). For comparisons of the Wong-Baker Faces Pain Rating Scale and SCASS scales, a repeated measures analysis of variance (ANOVA) will be used, considering the three groups and five time points of the study. This analysis will address the objective of comparing the effectiveness of interventions in controlling hypersensitivity over time. Post-hoc comparisons will be made using the Bonferroni adjustment to control for Type I error in multiple comparisons. The normality of the data distribution and the homogeneity of variance will be confirmed by the Shapiro-Wilk and Levene tests, respectively. The presence of sphericity will be verified using the Mauchly test, and if violated, corrections such as Greenhouse-Geisser will be applied. For secondary outcomes, repeated measures ANOVA will also be used to compare differences over time among the three intervention groups. Post-hoc analyses with Bonferroni correction will be applied when necessary. Effect sizes (partial eta squared) will be reported to assess the magnitude of differences between interventions. Additionally, Pearson or Spearman correlation coefficients will be used to explore associations between changes in hypersensitivity and secondary outcomes, depending on data distribution. Sensitivity analyses using an intention-to-treat approach may also be performed to assess the robustness of the findings. A significance level of 0.05 will be adopted for all analyses.

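### Enrolling 75 is a 13.6% increase over the required 66, not 15%, and covers a loss of at most 12% (9 children)

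*Protocol article*

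**What the plan says.** The Sample size calculation section of the protocol article uses G*Power "for a priori repeated measures ANOVA". The inputs are "An effect size of 0.352, derived from the group mean dispersions reported in the literature", alpha 0.05 and power 80%, and "the design includes 3 groups and 5 repeated measures". The result is stated as follows: "The final calculation indicates the need for 66 individuals in total, corresponding to 22 participants per group".

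The article then adds a margin, partly to offset dropout: "the sample will be inflated by 15%, resulting in 25 individuals per group and a total of 75 participants".

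Two other sections bear on this. Randomization fixes the total as five blocks of 15 with equal allocation. Clinical assessment classes a restoration with a C score on any modified USPHS criterion as a failure and removes that tooth from the study. Under Description of sample each child contributes one molar, so removing the tooth removes the child.

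**The concern.** A reader will take the 15% as the loss that the trial can bear while keeping its planned size. It is not. The figure was rounded down, and even an exact 15% increase would not protect against a 15% loss, because the loss applies to the larger enrolled number and not to the 66.

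What is at stake is a figure used in conduct and reporting. Over 12 months of follow-up, a team that believes it has 15% in hand would see no problem at 10 or 11 losses, although the margin is used up after 9. Any child withdrawn because the restoration failed draws on the same 9.

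**Working it through.** **Inputs from the article.** Evaluable total 66 (22 per group); stated inflation 15%; enrolled total 75 (25 per group); f = 0.352; alpha 0.05; k = 3 groups; m = 5 measures. **Not in the article:** the between-visit correlation ρ, and which effect of the repeated measures ANOVA was powered. Both are treated as assumptions below.

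**1. The stated inflation.**
- 22 × 1.15 = 25.3 per group; rounding up gives 26, the article has 25.
- In total, 66 × 1.15 = 75.9, so 76, or 78 with equal groups.
- Actual increase: 25/22 − 1 = 75/66 − 1 = 13.6%.

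**2. The loss that 75 can absorb.**
- 1 − 66/75 = 12.0%, which is 9 children, or 3 of 25 per group.
- At 15% loss: 75 × 0.85 = 63.75, so 63 or 64 remain.
- To keep 66 after 15% loss: 66/(1 − 0.15) = 77.6, so 78 (26 per group).

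**3. Reproducing the 66.** For the group main effect, the noncentral F has λ = f²·N·m / (1 + (m − 1)ρ) with k − 1 and N − k degrees of freedom. At ρ = 0.75 and N = 66:

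λ = 0.352² × 66 × 5 / (1 + 4 × 0.75) = 40.89/4 = 10.22, with 2 and 63 df; power 80.5%.

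In steps of three, the smallest N reaching 80% is 51 at ρ = 0.5, 66 at ρ = 0.75 and 69 at ρ = 0.8. The value 66 results for ρ from 0.713 to 0.761. So 66 can be reproduced on this reading, but ρ has been solved backwards from the answer.

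**4. What the shortfall does to power** (group main effect, f = 0.352):

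| ρ | N = 63 | N = 66 | N = 75 |
|---|---|---|---|
| 0.5 | 89.3% | 90.8% | 94.2% |
| 0.7 | 80.6% | 82.6% | 87.5% |
| 0.75 | 78.4% | 80.5% | 85.7% |
| 0.8 | 76.3% | 78.4% | 83.9% |

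With 64 children at ρ = 0.75, power is 79.1%. Power is at least 80% for ρ up to about 0.71 with 63 children, 0.73 with 64, 0.76 with 66 and 0.906 with 75.

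**5. The group-by-time test at the same f.** With λ = f²·N·m / (1 − ρ) and sphericity, the smallest N is 15 at ρ = 0.5 and 9 at ρ = 0.75, far below 66.

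**The case against.** The best defence is that the article describes a percentage increase on the calculated size, that 25.3 became 25, and that the difference is 0.3 of a child per group, or 75 against 75.9 in total. It nowhere promises that 66 will remain after a 15% loss, so the figure of 78 belongs to a convention that it does not claim. Power moves by about two points at most in the scenario that reproduces the 66.

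Much of that stands, and it sets the size of the point. It does not remove it. On the article's own rule 25 is still short of 15%, and the margin is given partly as cover for dropout, so the loss it really covers is the relevant figure.

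A reader might go further and infer three things that the article does not support.

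- *That the design does not deliver 80% power.* With f = 0.352 on the group main effect, 66 gives 90.8% at ρ = 0.5. It drops below 80% only above about 0.76, and 75 without loss only above about 0.906.
- *That 66 was computed for a different effect from the one to be tested.* The Statistical analysis section says "This analysis will address the objective of comparing the effectiveness of interventions in controlling hypersensitivity over time", but this echoes the first secondary objective, and the planned three-by-five ANOVA contains the group main effect. At the same f, the group-by-time test needs fewer children than 66.
- *That the missing correlation is itself an error.* The full protocol is a supporting file that is not shown, and the value may be there.

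On failed restorations, the article gives no expected failure rate, so how much of the margin they would use cannot be stated.

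**Conclusion.** The stated loss cover is wrong, by a small amount. Seventy-five children are 13.6% more than 66 and keep 66 only up to 12% loss; at 15% loss 63 or 64 remain, two or three below the stated requirement. This follows from the article's own numbers and needs no assumption.

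The consequence for power does rest on assumptions: the group main effect, f = 0.352, and a correlation of about 0.75. On these, 15% loss brings power to 78.4% to 79.1%. At a correlation of about 0.71 or below it stays at or above 80%. The point concerns a reported figure and leaves the adequacy of the trial's size untouched.

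**What to change.** In the Sample size calculation section, replace the 15% statement with one of two accurate ones: that 75 enrolled retains 66 evaluable children provided no more than 9 (12%) are lost, or that a 15% loss would leave about 63 to 64. Add that children who leave the hypersensitivity analysis because a failed restoration is removed from the study count towards the same 9.

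The cost is a sentence or two and a slightly less favourable figure. Enrolment can stay at 75. Going to 78 would gain little and would break the five blocks of 15 (78/15 = 5.2). The authors need not adopt any particular correlation or change the primary test on account of this point.

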### Randomization

The participants will be randomly allocated to the different groups using block randomization. A computer-generated sequence (random.org; Randomness and Integrity Services, Dublin, Leinster, Ireland) will be used to allocate each participant to a specific group maintaining a 1:1:1 proportion (equal number of participants in all groups). Randomization will be performed in 5 blocks, with 15 participants per block, totaling 75 participants across the study. Allocation concealment will be ensured with the use of sequentially numbered sealed opaque envelopes.

Teeth selected for treatment will be randomized into three groups:

**Group 1**: Photobiomodulation + restoration with self-cure composite resin

**Group 2**: Restoration with self-cure composite resin

**Group 3**: Photobiomodulation + restoration with photopolymerizable bulk-fill composite resin

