#### Group 3 – photobiomodulation + restoration with bulk-fill composite resin.

Initial periapical radiograph;Hypersensitivity reading (Wong-Baker Faces Pain Rating Scale for subjective pain of volunteer and SCASS for examiner’s assessment;Relative isolation (lip bumper, cotton roll and aspirator);Application of photobiomodulation;Selective removal of carious tissue with excavator, which involves complete removal of carious dentin from the surrounding walls followed by partial removal of softened dentin from the pulp wall (only Code 6 of MIH-SSS criteria);Selective etching of enamel adjacent to demarcated opacities with 35% phosphoric acid (Ultra Etch; Ultradent, Indaiatuba, SP, Brazil) for 20 seconds;Active application of universal adhesive (Ambar; FGM, Joinville, SC, Brazil) on dentin and enamel for 20 seconds (repeat procedure);Application of mild compressed air on adhesive for 5 seconds;Photoactivation for 10 seconds, peak of 1200 Mw/cm^2^ (Radii Cal; SDI, Melbourne, Vic, Australia);Restoration with Tetric N Ceram bulk-fill composite resin (Tetric N Ceram Bulk Fill; Ivoclar Vivadent, Barueri, SP, Brazil) with increments up to 4 mm, extending to demarcated opacities;Photoactivation for 20 seconds (Radii Cal; SDI, Melbourne, Vic, Australia);Clinical follow up after 48 hours and at four-month intervals for a period of 12 months (modified USPHS index);Hypersensitivity reading after 48 hours and at four-month intervals for a period of 12 months (Wong-Baker Faces Pain Rating Scale for subjective pain of volunteer and SCASS for examiner’s assessment).

The interventions will begin without an initial application of local anesthesia. The children will be informed that anesthesia is available and can be administered at any time during the procedure, if necessary.

A children’s toothpaste with 1100 ppm fluoride, which does not contain any components specifically designed for treating dentin hypersensitivity, will be provided to all participants. This toothpaste will be used for daily oral hygiene during the study to ensure consistency across all participants and avoid any confounding factors related to hypersensitivity treatment.

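### The planned ANOVA uses only group and time; adjusting for MIH-SSS code and baseline score would gain precision at little cost

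*Protocol article*

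**What the plan says.** **Eligibility.** The inclusion criteria admit both severity codes: "At least one permanent first molar with MIH (codes 5 and 6 of molar-incisor hypomineralization severity scoring system (MIH-SSS". The code is therefore known for each study tooth before allocation.

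**Procedure.** In the Clinical protocol for Groups 1 and 3, carious tissue is excavated in some teeth only, ending with "partial removal of softened dentin from the pulp wall (only Code 6 of MIH-SSS criteria". Group 2 follows the Group 1 sequence apart from the laser step, so all three arms mix excavated and non-excavated teeth.

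**Allocation.** The Randomization section states "The participants will be randomly allocated to the different groups using block randomization" and "Randomization will be performed in 5 blocks, with 15 participants per block, totaling 75 participants across the study", "maintaining a 1:1:1 proportion (equal number of participants in all groups". It names no stratification factor.

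**Analysis.** For both hypersensitivity scales, "a repeated measures analysis of variance (ANOVA) will be used, considering the three groups and five time points of the study". The five time points are the pre-treatment reading, 48 hours, and 4, 8 and 12 months, so baseline is one of the responses. "For secondary outcomes, repeated measures ANOVA will also be used to compare differences over time among the three intervention groups". No covariate is named in either place.

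**Severity as a predictor.** The Introduction says that hypersensitivity is more intense where the clinical manifestations are more severe. It also names poor adhesion to hypomineralised enamel as a main reason why restorations fail.

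**The concern.** The plan records a baseline factor, lets it determine part of the procedure, and treats severity in general as related to the primary outcome. It then omits the factor from the model. The blocks fix the number of children per arm but not the mix of codes within an arm. With 25 per arm, noticeable differences in that mix will be fairly common.

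Two things are at stake. First, if code predicts the post-treatment course, leaving it out puts its variation into the error term and widens the interval for every arm comparison, whether or not the arms happen to be balanced. Second, if the arms are unbalanced, the observed contrast carries part of the code effect, and an adjustment chosen after the imbalance is seen would be post hoc. Treating baseline as a fifth response also forgoes the precision that it would give as a covariate.

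**Working it through.** The plan gives no figure on this point, so there is none to reproduce. Inputs from the Protocol article are 25 children per arm, 1:1:1 allocation without strata, and five readings including baseline. Assumptions, because the article does not give them, are the code 6 share *p*, the size of the code effect, and a common within-child correlation *ρ*.

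**1. Chance imbalance between Groups 1 and 2.** The SD of the difference in code 6 share is √(2p(1−p)/25). A gap of 20 points is 5 teeth out of 25. Exact binomial probabilities:

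| p | SD of difference | Groups 1 and 2 differ by ≥ 20 points | Widest gap among three arms ≥ 20 points |
|---|---|---|---|
| 0.3 or 0.7 | √(0.42/25) = 0.130 | 16% | 34% |
| 0.5 | √(0.50/25) = 0.141 | 20% | 41% |
| 0.8 | √(0.32/25) = 0.113 | 11% | 24% |
| 0.9 | √(0.18/25) = 0.085 | 3% | 8% |

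**2. What an imbalance does.** Let code 6 add *c* to the score, and let the arms differ by *d* in code 6 share.
- If *c* is the same at all five readings, it drops out of every change from baseline. The group-by-time test is unaffected. The between-group main effect, which averages the five readings, shifts by d × c.
- If *c* acts only after treatment, the change-from-baseline contrast shifts by d × c. With d = 0.20 and c = 1 SD, that is 0.2 SD.
- Restoration longevity has no pre-treatment value, so nothing cancels there.

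**3. Precision of the Group 1 v Group 2 contrast.** Take the mean of the four post-treatment readings, residual SD 1, ρ = 0.5 and p = 0.5.
- Variance of that mean: (1 + 3×0.5)/4 = 0.625.
- Change score, no code effect: 0.625 + 1 − 2×0.5 = 0.625; SE = √(2×0.625/25) = 0.22.
- Change score, code shifts the post-treatment readings by 1 SD: add 0.5×0.5×1² = 0.25, giving 0.875; SE = √(2×0.875/25) = 0.26.
- Post-treatment mean with baseline and code as covariates: 0.625 − 0.5² = 0.375; SE = √(2×0.375/25) = 0.17. Simulation of the 3 × 25 design, which allows for estimating the coefficients, gives about 0.18.

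With no code effect, the whole gain comes from using baseline as a covariate. With a 1 SD post-treatment code effect, baseline alone leaves 0.375 + 0.25 = 0.625 (SE 0.22), and the code term brings the rest of the gain.

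Sensitivity to ρ, with no code effect: at ρ = 0.3 the change-score and covariate variances are 0.875 and 0.385 (SE 0.26 and 0.18); at ρ = 0.7 they are 0.375 and 0.285 (SE 0.17 and 0.15).

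**4. Power and type I error.** This is a simulation of a single reading, 25 v 25, true difference 0.8 SD, p = 0.5:

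| Code effect | Power without code | Power with code |
|---|---|---|
| 0 | 79% | 79% |
| 0.5 SD | 77% | 78% |
| 1.0 SD | 69% | 78% |

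Type I error was about 5% in every case, with and without adjustment.

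**The case against.** The strongest reply is that nothing here is invalid. An unstratified, unadjusted comparison in a randomised trial is sound, and covariate lists are often left to a fuller document; the article refers to a full protocol as a supporting file, which is not shown. The first part stands: type I error is unaffected. The second stands in part. Naming group and time does not formally exclude covariates, and if the full protocol lists code and baseline, the point is met. But the article is not silent on the model: it states the factors and makes baseline a response.

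Three further objections are right and limit the point.
- A reader might infer that a 20-point imbalance moves every arm contrast by a fifth of the code 5 v code 6 difference. It does not, because a constant code effect cancels from the group-by-time test.
- A single code term, on one degree of freedom, would not adjust that test. A code-by-time term is needed, and baseline cannot be both a response and a covariate.
- A reader might take the 41% in the table as the headline. It is the widest gap among three arms at a 50% share, where imbalance is greatest. The objectives speak of carious molars, and only code 6 teeth are excavated, so a high code 6 share is plausible and the risk could be much smaller.

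The Introduction also speaks of severity in general, not of code 5 against code 6, and every enrolled child must have hypersensitivity. The prognostic size of code in this sample is therefore unknown.

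**Conclusion.** The concern holds as a question of efficiency. The stated model omits a recorded, plausibly prognostic factor and uses baseline less efficiently than it could. The documents do not support the stronger readings that the comparison is biased, that its error rate is inflated, or that the randomisation is defective.

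On the assumptions above (ρ = 0.5, half the teeth code 6), adjustment would cut the standard error of the Group 1 v Group 2 contrast from 0.22–0.26 SD to about 0.18 SD, with no loss if code proves irrelevant. Much of that comes from baseline. The contribution of code itself ranges from nothing to substantial, depending on how far it alters the post-treatment course. The case for acting is this asymmetry: little to lose, and a worthwhile gain if code matters. It is a cheap improvement.

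**What to change.** Before any outcome data are compared by arm, specify the hypersensitivity analysis as a model of the four post-treatment scores (48 hours, 4, 8 and 12 months) with group, time, group-by-time, baseline score, MIH-SSS code (5 or 6) and code-by-time. Include code in whatever analysis is used for restoration longevity. Report the code mix by arm. Leave the randomisation, sample size and clinical procedures as they are.

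The cost is one degree of freedom for baseline, one for code and three for code-by-time (four time points less one), with a modest restructuring of the planned ANOVA because baseline moves from response to covariate. No new data are needed.

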### Blinding

All treatments across the three groups will be carried out by a single operator, who will have completed training and calibration sessions during the initial phase of the study. Clinical assessments after 48 hours as well as four, eight and twelve months after treatment (follow-up) will be performed by an examiner blinded to allocation (single-blind study). The operator and examiner will undergo previous calibration exercises, evaluating approximately 20 cases, with the calculation of the Kappa statistic to ensure greater than 85% inter-observer agreement. The calibration will follow the criteria of the modified index of the United States Public Health Service (USPHS) [24,25] and the MIH-SSS diagnostic criteria [20]. The data will be analyzed by a blinded statistician.

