#### Group 2 – restoration with self-cure composite resin.

Same as previous sequence (Group 1) with exception of Item 3.

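### A single published block size of 15, with one unblinded operator treating every child, means sealed envelopes alone cannot guarantee concealment: about 7 of 75 allocations can be deduced by counting

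*Protocol article*

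**What the plan says.** The protocol article's Randomization section sets one block size: "Randomization will be performed in 5 blocks, with 15 participants per block, totaling 75 participants across the study". Allocation is by "maintaining a 1:1:1 proportion (equal number of participants in all groups"), which gives five places per arm in every block. On concealment it states: "Allocation concealment will be ensured with the use of sequentially numbered sealed opaque envelopes". It does not say that block sizes vary or are withheld.

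The Blinding section states: "All treatments across the three groups will be carried out by a single operator". The people blinded are the follow-up examiner ("performed by an examiner blinded to allocation (single-blind study")) and the statistician. The operator is not among them and could not be:

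- The Group 2 procedure is described as "Same as previous sequence (Group 1) with exception of Item 3", and the omitted item is the laser.
- Group 3 is "Photobiomodulation + restoration with photopolymerizable bulk-fill composite resin", which adds acid etching, a different adhesive and light curing.

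On timing, the Description of sample section states: "Individuals who met the eligibility criteria will immediately be randomized and treated".

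**The concern.** A sealed opaque envelope hides the card inside it. It does not hide what follows from the earlier cards once the block size is known. When two arms have each used their five places, the rest of the block must go to the third.

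The operator sees every allocation in order, because the operator carries each one out and treatment follows randomization at once. The block size is in print. The envelopes, the only safeguard named, therefore leave some allocations open to deduction, and the wording promises more than the method delivers.

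What is at stake is selection before allocation. Some entry criteria need judgement: whether hypersensitivity is present, whether the tooth can be seen and reached directly, and whether the defect is too extensive for a direct restoration. If someone who foresees the next arm can influence these decisions, or when a child is brought in, milder or more severe teeth could be steered towards an arm. A blinded examiner at 48 hours and at 4, 8 and 12 months would not undo that, because the groups would already differ at entry.

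**Working it through.** **Inputs.** Five blocks of 15 and 1:1:1 allocation (Randomization); one operator for all arms (Blinding); arms distinguishable to the operator (Group 2 and Group 3 procedures); treatment immediately after randomization (Description of sample). Assumption: the person knows the block size and counts correctly.

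**The plan's own figures.** 5 × 15 = 75. 15/3 = 5 per arm per block, and 5 × 5 = 25 per arm. These reproduce.

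**Allocations known with certainty.** An allocation is certain once the other two arms are used up in the block. Any one of an arm's five places comes after all ten places of the other two arms with probability 1/11. The expected count is 5/11 per arm, and over three arms:

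- 3 × 5/11 = 15/11 = 1.36 per block
- 5 × 15/11 = 6.82 of 75, or 9.1%

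Cross-check through the length of the final same-arm run: 1 + 4/14 + (4·3)/(14·13) + (4·3·2)/(14·13·12) + (4·3·2·1)/(14·13·12·11) = 1 + 0.2857 + 0.0659 + 0.0110 + 0.0010 = 1.364. The last allocation is thus certain in every block (at least 5 of 75), the last two in 28.6% of blocks, and the last three in 6.6%. A simulation of 200,000 blocks gave a mean of 1.365.

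**Allocations with exactly one arm ruled out.** After a given arm is used up, each of the ten other places remains with probability 1/6, so the expected number remaining is 10/6. Summing over three arms gives 5. Subtracting the places counted twice (15/11) leaves 40/11 = 3.64 per block with at least one arm excluded. Removing the certain ones:

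- 40/11 − 15/11 = 25/11 = 2.27 per block
- 5 × 25/11 = 11.4 of 75

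For these, two arms remain possible, so they are narrowed but not foreseen.

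**Effect of block size.** For a known fixed block with n places per arm, the certain count is 3n/(2n + 1) per block. Multiplying by 75/(3n) blocks gives 75/(2n + 1) in all:

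- size 3: 75/3 = 25.0
- size 6: 75/5 = 15.0
- size 9: 75/7 = 10.7
- size 12: 75/9 = 8.3
- size 15 (the plan): 75/11 = 6.8

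A shorter fixed block would be worse.

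**With varying, undisclosed sizes.** Counting within a block gives no certainty if only the total of 25 per arm is known. What remains is the final run of the last block. Using 3n/(2n + 1), this is 9/7 = 1.29 allocations if the last block has 9 places and 21/15 = 1.40 if it has 21.

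**The case against.** The strongest objection is that the step from foreknowledge to bias is not in the document. The article gives the operator the treatments. It does not say that the operator recruits, judges eligibility, schedules children, holds the list or opens envelopes. The Hypersensitivity assessment section has both operator and examiner using the cold-air scale, whereas the group procedures call that reading the examiner's, so the operator's part at baseline is unsettled. The full protocol (S2 File) is not shown and may cover these roles. This objection stands: selection bias is a possibility that depends on a role the article does not state.

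The size is also modest. Fifteen is a long block. The certain allocations average 6.82/3 = 2.27 per arm of 25. As an illustration only, suppose every one of them were exploited and baseline severity in those children shifted by 0.5 to 1 SD. One arm's mean would then move by 2.27/25 × 0.5 = 0.05 SD to 2.27/25 × 1 = 0.09 SD.

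Three stronger readings are tempting but unsupported:

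- **A quarter of the trial is foreseeable.** The sum 6.8 + 11.4 = 18.2 of 75 (24%) mixes known allocations with ones where two arms are still open.
- **The no-laser group is hit hardest.** In a 5/5/5 block the arms are exchangeable, so each is equally likely to fill the final run.
- **The order of tooth choice and randomization is unsafe.** The Description of sample section already places eligibility and the tooth lottery before randomization.

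Nor is it a fault that the article omits who prepares the list, since an article commonly leaves that to the full protocol.

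None of this rescues the claim that envelopes ensure concealment. The fixed, disclosed block size is a stated choice, not a missing detail.

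**Conclusion.** The concern holds in a limited form. With a fixed, published block of 15 and an operator who sees every allocation in sequence, sealed envelopes alone do not guarantee concealment. On average 6.8 of 75 allocations (9%), and never fewer than 5, can be deduced with certainty. For about 11 more, one arm can be excluded. This rests on someone knowing the block size and keeping an accurate count.

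A reader might infer that selection bias will occur. The documents do not support that, because they do not show that the person who can count also influences enrolment or its timing. If so, the bias is possible and blinded follow-up would not remove it. The change is worth making because it is cheap and closes most of the gap.

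**What to change.** Replace the five fixed blocks of 15 with permuted blocks of varying size, in multiples of three and in random order, that sum to 75. If no envelope has been used, 9, 12, 15, 18 and 21 is one example: 9 + 12 + 15 + 18 + 21 = 75, with 3 + 4 + 5 + 6 + 7 = 25 per arm. If envelopes have been used, choose sizes that fit the remaining places and change over at the end of a block. After one block of 15, for instance, 9 + 12 + 18 + 21 = 60.

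Withhold the sizes and their order from the operator and others with patient contact, and state publicly only that block sizes vary. Do not shorten the block to another fixed, known size.

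The cost is regenerating the list and the unused envelopes. Sample size and final 1:1:1 balance are unchanged. Arm balance part-way through recruitment can be slightly looser within the larger blocks.
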